### Analysis plan

This study will primarily be descriptive and exploratory in nature, as we expect to find small numbers of cases of NPH. We will proceed through the approach described below and will consider additional analyses depending on our findings.

For any hypotheses, we will create Directed Acyclic Graphs to guide our models and decide which measures to include as likely confounders, effect modifiers, or mediators. For all analyses, when relevant we will present data disaggregated by sex, due to the documented increased risk of NPH among males.

### Validation of automated CA measure

The algorithm for measurement of CA shared by [name]
*et al.*
^
34
^ has been validated in several research populations but never in a routine clinical population. We will therefore conduct validation of this measurement in our sample.

A subsample of brain MRIs (n= 100) will be visually assessed and have CA manually measured by a Consultant Neuroradiologist with expertise in NPH (SI) and will be blinded to the automatic measurement result. The lead author ([name]) will receive training to measure CA and will manually measure the same subsample of scans as a second rater. Native scans will be loaded into 3D Slicer
^
68,
69
^, an open-source imaging platform. The anterior (AC) and posterior (PC) commissures will be identified visually, and scans will be transformed to align with the AC-PC line. CA measurement will be performed at the perpendicular plane, at the level of the PC, according to convention
^
31,
70
^. We will ensure consistent technique through careful training. We will randomly select cases and purposively sample outliers for the comparative sub-sample.

Inter-rater and intra-rater reliability will be calculated for the manual measurements of CA. Inter-rater reliability of CA has been shown to be high in other studies
^
29
^.

Manual measurements will be compared against those generated automatically using linear regression and a Bland-Altman plot to assess agreement between the two methods. The range and variability of both methods will be compared, along with their respective errors. Convergent validity of CA will be investigated by examining its correlation with other imaging biomarkers of NPH, as defined by Kockum’s Radscale
^
29
^, such as ventriculomegaly and WMH.

We will use logistic regression to examine for systematic differences (eg. demographics, primary diagnosis) between people for whom SynthSeg and CA measurement fails and those for whom it is successful, to examine for systematic bias.

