### Memory services

No study has so far explored the role of memory services in assessing people with possible NPH in England, though these are an important source of referrals for NPH clinics
^
41
^. To the best of our knowledge, only one study has examined imaging features of NPH in a memory clinic population
^
38
^.

Electronic health record (EHR) studies of NPH are limited by the possibility of false negatives in recorded diagnoses, due to suspected under-diagnosis of NPH
^
12,
22
^. There is a need to further our understanding of clinical and radiological features suggestive of NPH in clinical populations. In addition, we lack normative data regarding NPH imaging features in clinical populations, which is key when considering the development of screening tools for this condition.

We therefore propose the first study of NPH and its clinical and radiological features in memory clinics in the UK. Little is known about this topic and this study will provide an initial exploration of a neglected area of research. NPH is a rare outcome, with an expected prevalence of 1% in memory services
^
38
^. Due to the uncertainty surrounding recorded diagnosis of NPH, and the frequent co-occurrence of NPH with other neurodegenerative conditions
^
42
^, this study will also examine for the first time whether imaging features of NPH are independent predictors of outcomes, and whether they are associated with prognosis in other diagnoses such as AD and Parkinson’s disease.

Untreated NPH is associated with a higher risk of dementia and death than the general population
^
43
^. If CA or other imaging markers are validated as a reliable measure for this population, these could be developed as automated decision-support tools for NPH, with the potential to benefit both individuals and healthcare systems. Though shunting is not appropriate or effective for all, it could alleviate symptoms and reduce long term costs in a potentially large number of people with cognitive decline. The possibility to prolong independence and potentially delay dementia onset at a time when global dementia cases are unprecedentedly high and set to increase
^
44
^, makes study of NPH a priority.

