### Study design

We will assemble a retrospective cohort study using SLaM’s CRIS data platform. The study population will be all people aged 60 years and above with at least one referral to memory services recorded over the study period 2007–2024. We expect at least 20,000 participants in this cohort. We will extract relevant anonymised retrospective patient data from CRIS for the entirety of the cohort and specify the data extraction date. We will examine CRIS data and use linkage data to HES, ONS, and imaging data.

A subset of this cohort will have linked T1-w, T2-w, and FLAIR brain MRI scans that have been collected as part of routine clinical care over the period 2008–2021. We expect to have at least 5,000 people in this sample, based on the number of scans currently available, however the sample size is subject to change as these datasets are live.

*Inclusion criteria:*

Aged at least 60 years at time of memory clinic referralReferral to memory services, recorded in CRISPeople who are referred but do not attend a review will be included and compared with those who do attend, though they may have limited data

*Exclusion criteria:*

Nil

*Cohort entry date:*

Date of referral to memory service

*Exit from cohort:* Censored at minimum of

DeathIncident NPH diagnosisEnd of study period

*Covariate assessment window:*

Anytime prior to cohort entry date up to three months after date of first face-to-face or virtual review in memory clinic, inclusive

*Primary outcome:* ICD10 code G91.2 recorded in CRIS
*or* HES
*or* ONS,
*or* context-confirmed NPH recorded in CRIS

*Possible secondary outcomes:*

MortalityHospitalisation profileDementia diagnosisCognitive trajectorySymptoms of NPH (eg. falls)

*Exposures:*

CA in degreesVentricular volume in mm
^3^
White matter hyperintensities (WMH) volumesOther brain measures to be determined (TBD)

*Possible covariates:*

AgeSexEthnicityIMDRisk factors for NPHCognitionHealth of the Nation Outcome Score (HoNOS)

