There is a risk that the CA measurement tool will not correspond to manual measurements in our population. This is unlikely, as it has been shown to perform well in several research populations
^
34
^. However, if this happens, we will consider adapting the existing algorithm (eg. altering its measurement pitch). In addition, we plan to include a range of imaging measures, some of which are available from existing SynthSeg output (eg. ventricular volume). A strength of our study is that all participants will have imaging undertaken based on clinical need, therefore using similar selection processes, and from the same imaging centre and single scanner make and sequence.

NPH is rare, which may limit our analyses. However, the study only requires 5 cases of NPH to test for a mean difference in CA and feasibility counts suggest we will have enough cases. In addition, we plan a range of analyses, many of which are primarily descriptive. This study will provide a first descriptive overview of the distribution of imaging features of NPH in a UK memory clinic population and how this varies with pre-specified covariates.

Findings in London memory services may not be generalisable to the whole of the UK or to NPH in other services. In particular, memory complaints will be significantly represented in these services, which may not be typical for NPH, which often presents with gait disturbance. However, we are seeking to explore NPH presentation in under-represented samples and seeking to work out if people are missed in these other settings because of different presentations. In addition, these services have the strength of providing a first assessment of NPH in a diverse population. Though there are many benefits to using routine clinical data, one significant drawback is the lack of a systematic approach to assessment of patients. As a result, data may be missing or incomplete due to differing clinical practice between practitioners. Data will only be available according to clinicians’ assessments, which may introduce bias and unmeasured confounding into our study. We will assess for differences between groups as we proceed through the study, to look for possible systematic biases in data collection.

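### The callosal-angle validation sample mixes random scans with chosen outliers and, read plainly, analyses them together, so its agreement figures would not estimate agreement in the routine cohort

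*Protocol article*

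**What the plan says.** All of this is in the protocol article.

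- **Aim.** Validation of automated CA measure notes that the algorithm has been validated in research populations but not in a routine clinical one, and continues: "We will therefore conduct validation of this measurement in our sample". Study design describes the imaging subset: "We expect to have at least 5,000 people in this sample".
- **Sample.** "A subsample of brain MRIs (n= 100) will be visually assessed" by a neuroradiologist blinded to the automated result, and a second rater measures the same scans. On selection: "We will randomly select cases and purposively sample outliers for the comparative sub-sample".
- **Analysis.** "Manual measurements will be compared against those generated automatically using linear regression and a Bland-Altman plot to assess agreement between the two methods". Also: "The range and variability of both methods will be compared, along with their respective errors". Inter-rater and intra-rater reliability of the manual readings are to be calculated as well.
- **Use.** Strengths and limitations considers the case in which the tool does not correspond to manual measurement: "However, if this happens, we will consider adapting the existing algorithm (eg. altering its measurement pitch").

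The article does not say how many of the 100 scans are random, what counts as an outlier for this selection (extreme angle, suspected failure or large discrepancy), or whether the two kinds of scan are analysed apart or weighted.

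**The concern.** Limits of agreement are the mean difference plus or minus 1.96 standard deviations of the differences. They describe a population only if the scans represent it or are weighted back to it. Purposively chosen outliers enter with an unknown and much higher probability than other scans.

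Two distortions follow, and they need not point the same way. If the outliers are enriched for algorithm failures, the limits widen. If they are enriched for true extremes of angle, the spread of values grows, so the correlation rises and the slope shifts while the limits hardly move. The planned comparison of range and variability is set directly by the selection.

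This would be the tool's first validation in routine scans, and CA is the first exposure listed under Study design. A reader would take the published limits as the error to expect in ordinary memory-clinic scans. Pooled figures could make a serviceable tool look poor, or make the association between methods look tighter than it is.

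**Working it through.** The article states no limits of agreement, no target precision and no derivation of n = 100, so there is no printed figure to reproduce. The check asks how far pooled figures could sit from cohort figures.

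**Inputs from the article.** Cohort 5,000; sub-sample 100; NPH prevalence 1% ("NPH is a rare outcome, with an expected prevalence of 1% in memory services"); CA mean 66 (SD 14) in NPH and 104 (SD 15) in Alzheimer's disease (Sample size and power calculation). The Alzheimer's values stand in for all non-NPH scans.

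**Assumed, not in the article.** Ordinary error SD of the difference 5 degrees; gross failures in 0%, 3% (SD 25) or 5% (SD 30) of scans; outliers drawn from the most extreme 3%, either by automated CA or by automated-minus-manual difference; 20 outliers in 100 unless stated.

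**Step 1: true cohort limits**, 1.96 × √(variance of the differences).

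- No failures: 1.96 × 5 = ±9.8.
- 3% failures: 1.96 × √(0.97 × 25 + 0.03 × 625) = 1.96 × √43.0 = ±12.9.
- 5% failures: 1.96 × √(0.95 × 25 + 0.05 × 900) = 1.96 × √68.75 = ±16.3.

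**Step 2: pooled limits**, 80 random + 20 outliers, 400 simulated cohorts per setting.

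| Gross failures | Cohort | Pooled, chosen on automated CA | Pooled, chosen on difference | Random scans only |
|---|---|---|---|---|
| 0% | ±9.8 | ±10.2 | ±14.2 | ±9.8 |
| 3% | ±12.8 to ±12.9 | ±19.8 | ±25.3 | ±12.3 to ±12.5 |
| 5% | ±16.3 | ±30.2 | ±36.5 | ±15.8 to ±16.0 |

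One cell can be checked by hand. With no failures and choice on the difference, the top 3% lies beyond 2.17 SD, where the mean squared difference is 6.48 × 25 = 162. Pooled: 1.96 × √(0.8 × 25 + 0.2 × 162) = 1.96 × √52.4 = ±14.2.

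With 10 outliers instead of 20 and 3% failures, the pooled limits are ±16.5 (automated CA) or ±20.1 (difference).

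**Step 3: how much the outlier rule matters.** Keep 3% failures and 20 outliers chosen on automated CA, but split the ordinary error into automated SD 4 and manual SD 3 (√(16 + 9) = 5). The true limits are again ±12.9. Pooled limits:

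- the 20 most extreme of 5,000 (top 0.4%): ±32.9
- 20 from the top 3%: ±19.9
- 20 from the top 5%: ±18.0
- 20 from the top 10%: ±15.3

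The slope of manual on automated CA, 0.87 in the cohort, falls to 0.64 under the top-20 rule and to 0.80-0.86 under the other three. With 1% failures and the top-3% rule, the limits are ±14.3 against ±10.9.

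**Step 4: correlation and slope** (Step 2 model; slope of automated on manual). Chosen on automated CA with no failures, r rises from 0.951 to 0.977 and the slope from 1.00 to 1.05. Chosen on the difference with 3% failures, r falls from 0.92 to 0.77. The simulated errors are symmetric, so the mean difference is not displaced; failures leaning one way would shift it too.

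**Step 5: precision given up by using random scans only.** The 95% half-width of a limit, in SDs of the difference, is 1.96 × √(1/n + 1.96²/(2(n − 1))).

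- n = 100: 1.96 × √(0.0100 + 0.0194) = 0.34.
- n = 80: 1.96 × √(0.0125 + 0.0243) = 0.38.

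**The case against.** **Pooling is not stated in so many words.** This is right. The article is condensed, and a fuller plan could compute limits with and without the outliers. A reader might infer that the protocol commits to pooled statistics; the text supports that only as its plain reading, because one sub-sample is followed by one regression and one plot. The point is still more than missing detail: the article does state the sampling and the analysis, and followed as written the two together do not give an estimate for the cohort.

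**The large figures depend on assumptions.** This is also right. About ±33 requires the 20 most extreme scans of 5,000 and 3% gross failures, and neither is in the documents. Study procedure excludes poor scans, inspects every segmentation and uses the software's own quality control. The validation section also examines measurement failures separately by logistic regression. Some failures would therefore be gone before agreement is assessed, although the angle is computed after segmentation and angle errors can survive. Without failures, and with outliers chosen on automated CA, the limits barely move.

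**Correlation is not the planned agreement statistic.** True. The correlation named in that section concerns other imaging markers. An inflated r matters only if it is reported from the regression, and the Bland-Altman plot guards against relying on it.

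**No decision rule misfires.** A reader might infer that this validation determines whether the algorithm is used. The article says only that adaptation will be considered, sets no cut-off, and describes the study as mainly descriptive and exploratory. What is at stake is a misleading description of measurement error.

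**Sampling outliers is good practice.** It is, for finding failure modes. A random 100 is also thin at low angles: with Table 3's sensitivity of 97%, specificity of 88% and 1% prevalence, (50 × 0.97 + 4,950 × 0.12)/5,000 = 12.9%, so about 13 scans below 90 degrees and about 1 NPH case. Enrichment is reasonable; the fault is the absence of a separate or weighted analysis.

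**Conclusion.** The point holds in this form: a sub-sample partly random and partly chosen for being outlying, analysed as one, gives limits of agreement, slope and range that reflect the sampling mix as well as the tool, and does not estimate agreement in the routine cohort. Rater reliability computed on the same scans shares the problem.

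The direction is uncertain and the size cannot be fixed from the documents, because the share of outliers and the rule for choosing them are not given. On the assumptions above, the limits run from almost unchanged to roughly two and a half times too wide (32.9/12.9 = 2.6) at 3% failures. The upper end should not be read as the expected result. The pooling rests on the plain reading of the text.

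**What to change.** In Validation of automated CA measure:

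1. State how many of the 100 scans are drawn at random and define an outlier for this selection.
2. Compute bias, limits of agreement, regression and inter- and intra-rater reliability on the random scans only.
3. Report the purposively chosen outliers separately as a review of failure modes, for instance marked on the plot but left out of the limits.

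If more information is wanted at small angles, an alternative is to sample at random within strata of automated CA, record the sampling fractions, and weight the agreement statistics by their inverse. This is an option and not a necessity.

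Either route keeps the same 100 scans and the same readers. The cost is some wording and slightly wider confidence intervals on the limits, as in the last step of the working (0.38 SD with 80 random scans against 0.34 SD with 100). If separate analysis is already intended, one sentence saying so settles the point.

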### Descriptive analyses

We will calculate the period prevalence of recorded diagnoses of NPH in our sample, as defined in
Table 2. We will define NPH diagnosis as ICD10 code G91.2 recorded in CRIS or HES or ONS, or context-confirmed NPH recorded in CRIS.

We will describe the distribution of imaging features of NPH in this population and produce summary statistics. This will include examining for normality and calculating the mean or median of these measures in the population. We will visualise the data and categorise the data into quartiles or quintiles, where appropriate. We will take a dimensional approach, considering these measures as continuous and categorical variables.

We will examine the association between CA and other brain measures of NPH. We will examine the association between imaging features of NPH and markers of neurodegeneration, such as cortical atrophy and hippocampal volume. We will describe the period prevalence of imaging features suggestive of NPH, based on reported cut-offs.

We will describe variation in CA and other imaging features of NPH according to demographics, covariates, and risk factors for NPH (see
Table 2).

We will describe imaging features of NPH in relation to recorded diagnosis of NPH. We will describe the relationship between imaging features and diagnosis of NPH, including whether a clinically useful threshold exists. We will build several models to examine individual imaging features of NPH and combinations of features, to assess for possible additive effects of these. In addition, we will compare clinical radiological reports, which are available in the free text notes of CRIS, with imaging features of NPH to look for concordance of these findings and to determine what role the imaging report played in future management of these cases.

We will examine for systematic differences based on EHR data between individuals with and without imaging data in the cohort using logistic regression.

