^ and is a live data resource, updating against the source EHR every 24 hours. CRIS data have been linked with a range of external sources within a trusted research environment, including all hospitalisations in England (via Hospital Episode Statistics (HES) provided by NHS England) and Office of National Statistics (ONS) mortality and 2011 Census data
^
52
^. Lambeth primary care datanet has additional linkage to CRIS.

CRIS provides linkage to routinely-collected neuroimaging data through the SLaM Image Bank. Full details of the linkage procedure for this have been described elsewhere
^
53
^. The scans used in this study have primarily been carried out on a General Electric (GE) 1.5T HDx model scanner. SLaM images are stored on a secure [name]'s College London server as de-identified raw images, unlinked from clinical information. This server is known as the neuroimaging analytics network. The neuroimaging network is a secure Kings’ College London platform with high performance cluster capacity, which is accessed following appropriate approvals.

Data preparation and curation will be carried out for EHR clinical data and neuroimaging data through separate procedures, as described below.

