**Outcomes**			
*Diagnosis of NPH*	ICD10 code G91.2 or context-confirmed description of diagnosis of NPH in medical record	CRIS or HES or ONS	Medical record
*Dementia diagnosis*	ICD F00-03 diagnosis on or closest after index date	CRIS or HES or ONS	Medical record
*Cognitive trajectory*	All additional recorded MMSE scores at least three months after index MMSE, until censoring occurs	CRIS	Medical record
*All cause mortality*	First date of death recorded after index date	CRIS	Medical record
*Cause of death*	Recorded primary cause of death based on death certificate	ONS	ONS data
*Hospitalisation profile*	Date and diagnosis associated with hospital episode	HES	Medical record

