### Potential further analyses

Depending on our initial exploratory findings, we will consider additional analyses. If we have sufficient cases of individuals with imaging features of NPH, we plan to undertake additional statistical analyses, such as Cox regression with time to mortality or dementia diagnosis as outcomes.

If we have sufficient cases, we will describe NPH imaging features in relation to outcomes such as hospitalisation, mortality, cognitive decline, and dementia diagnosis. We will describe hospitalisation profiles (eg. falls, surgery) in relation to NPH imaging features. We will look at factors associated with subsequent diagnosis compared to no diagnosis among people with imaging features of NPH.

If, as expected, we find few cases of NPH, we will define NPH ‘imaging cases’ based on the presence of suggestive imaging features and their relationship with NPH diagnosis, and consider a nested case-control study. We will assess for differences in risk factors, demographics, and clinical covariates (see
Table 2) between cases and controls using logistic or categorical regression.

We plan to test our measures in low-field MRI
^
72
^, and we will consider comparing our findings in other datasets
^
73
^.

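### NPH or dementia found only in ONS death records can be dated only at death, so mortality effects would enter any time-to-diagnosis model (a minor point, mainly for dementia)

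*Protocol article*

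**What the plan says.** **Outcome sources.** The primary outcome in Study design begins "ICD10 code G91.2 recorded in CRIS" and goes on to accept HES or ONS as alternatives, plus context-confirmed free text in CRIS. Descriptive analyses repeats this: "We will define NPH diagnosis as ICD10 code G91.2 recorded in CRIS or HES or ONS, or context-confirmed NPH recorded in CRIS". Table 2 defines dementia as "ICD F00-03 diagnosis on or closest after index date", and for both NPH and dementia it gives the data source as "CRIS or HES or ONS". ONS alone is therefore enough for either outcome.

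**What ONS holds.** Study population and setting describes the linkage as "Office of National Statistics (ONS) mortality and 2011 Census data". A census carries no ICD-10 diagnosis of this kind, so an ONS diagnosis code comes from a death record.

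**Follow-up.** Study design ends follow-up under the words "Censored at minimum of", followed by three list items that run together in the text: "DeathIncident NPH diagnosisEnd of study period".

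**Time-to-event use.** Diagnostic accuracy of CA would consider Cox regression, possibly penalised, for NPH if numbers suffice. Potential further analyses would add models "such as Cox regression with time to mortality or dementia diagnosis as outcomes", again depending on numbers. The Abstract also hypothesises that imaging features predict a later NPH diagnosis.

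**The concern.** One outcome definition serves two purposes. For the question of whether a diagnosis was ever recorded, a death certificate is a legitimate source. For the question of when a diagnosis was made, it is a poor one. The recorded time is the time of death, and only people who die can be found by this route.

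In a Cox model for time to diagnosis, anything that raises mortality then also raises the apparent rate of diagnosis. A marker could look predictive of dementia because it is related to death. The definition is stated without restriction by type of analysis, so followed as written it would carry over into these models.

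**Working it through.** **Inputs from the protocol**
- Scanned subset: 5,000 people, expected NPH prevalence 1% (Table 3). 0.01 × 5,000 = 50 cases, which matches the 50 in Table 3.
- ONS-only share of events, and the effect of any marker on death: not given. Both are assumed below and shown as ranges.

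**Formula.** Let the marker have no effect on diagnosis in CRIS or HES (hazard λ), and let it multiply the death hazard μ by HR_death. Let a fraction c of deaths without a prior record carry the code on the certificate, whatever the marker status. If these deaths count as events:
- marker-negative hazard = λ + cμ
- marker-positive hazard = λ + cμ × HR_death
- ONS-only share of events in the marker-negative group: s = cμ / (λ + cμ)
- apparent HR = (1 − s) + s × HR_death, where the correct value is 1.00

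**Results**

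| s | HR_death 1.5 | HR_death 2.0 |
|---|---|---|
| 5% | 0.95 + 0.05 × 1.5 = 1.025 | 0.95 + 0.05 × 2 = 1.05 |
| 10% | 0.90 + 0.10 × 1.5 = 1.05 | 0.90 + 0.10 × 2 = 1.10 |
| 20% | 0.80 + 0.20 × 1.5 = 1.10 | 0.80 + 0.20 × 2 = 1.20 |

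**Check by simulation.** Cox models were fitted to 20,000 simulated people, 6 repeats per setting, with no true effect on diagnosis. The HR with ONS-only events counted, divided by the HR without them, was:
- s = 10%: 1.070/1.011 = 1.06 (HR_death 1.5) and 1.060/0.961 = 1.10 (HR_death 2)
- s = 20%: 1.124/1.011 = 1.11 and 1.220/1.012 = 1.21

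These agree with the formula.

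**Size for dementia.** A second simulation used 5,000 people, 25% marker-positive, death hazard 0.08 and dementia hazard 0.07 per year, and censoring at 3 to 16 years. The SE of the log HR was 0.05 to 0.06.
- s = 10%, HR_death 1.5: ln 1.05 = 0.049, or 0.8 to 1.0 SE
- s = 10%, HR_death 2: ln 1.10 = 0.095, or 1.6 to 1.9 SE

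**Size for NPH.** With at most about 50 events and an assumed 25% marker-positive, SE ≈ √(1/(50 × 0.25 × 0.75)) = √(1/9.375) = 0.33.
- s = 10% is 5 cases. The same shifts of 0.049 and 0.095 are 0.049/0.33 = 0.15 SE and 0.095/0.33 = 0.29 SE.

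**The case against.** **The affected models are not committed.** Analysis plan describes a mainly descriptive study. NPH is compared by a t-test or Mann-Whitney test and by logistic regression; both Cox analyses depend on numbers. Event dating in a conditional model may also be settled in a fuller analysis plan. This stands, and it limits the weight of the point.

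**The prevalence definition is not wrong.** The sentence in Descriptive analyses serves period prevalence, where a death-certificate case belongs. This stands too. The difficulty arises only when the Study design and Table 2 definitions are carried into time-to-event models.

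**There is no real clash between event and censoring.** A reader might infer that an ONS-only case is both an event and censored on one day, so that the protocol contradicts itself. The exit list does not support that. It also names incident NPH diagnosis, which is the primary outcome; read literally, no NPH event could ever occur. The list means end of follow-up, and someone whose outcome falls on the exit date is an event. The dating problem remains after that reading.

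**Certificate-only codes may be genuine disease.** The formula treats them as unrelated to the marker. Memory services (Introduction) names missed diagnoses as a limit of health-record studies, so dropping these cases loses some true ones. This stands, and it is why both versions should be shown.

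**Conclusion.** The point holds as a minor one. The stated definitions let a death record count as an incident diagnosis dated at death, and any time-to-diagnosis model built on them would absorb part of the mortality effect. The spurious HR is 1.05 to 1.10 at a 10% ONS-only share and 1.10 to 1.20 at 20%, for death HRs of 1.5 to 2. The share, the death HR and the simulated event rates are all assumptions. Nothing in the protocol shows that the share is as high as 20% in people already referred to memory services.

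For dementia, a possible secondary outcome, the shift is around one SE or more if the share exceeds about 10%. For NPH in the scanned subset it is a small fraction of an SE.

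A reader might infer that the bias favours the study's main hypothesis, because the Introduction links untreated NPH with a higher risk of death. The documents do not support that. The stated hypotheses concern NPH diagnosis and CA, where about 50 expected cases make the shift negligible.

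**What to change.** 1. Keep ONS in the ever-recorded definition used for period prevalence.
2. For time-to-event models, and for any claim about future diagnosis, date the event by the first record in CRIS or HES.
3. Treat people whose only record is in ONS as deaths without a prior recorded diagnosis, at the date of death.
4. Report how many such people there are, separately for NPH and dementia.
5. Show the model that counts them as events beside the CRIS/HES version.

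The cost is a sentence in the outcome definition and one extra run of each model on data already linked. The CRIS/HES version has slightly fewer events and misses some disease that was never diagnosed in life. Reporting both versions makes that visible and shows whether the issue matters in these data.
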